### 2.7. Intervention

An online and offline (OTO) intervention for PPD prevention among rural-to-urban floating women, called the “Hi, Mom” program, was developed using the theoretical framework incorporated self-efficacy theory [51] and social exchange theory [52]. Sound evidence identified that appropriate levels of self-efficacy and social support are essential components of interventions to improve patients’ symptom management [23]. The “Hi, Mom” program is designed to enhance women’s self-efficacy and social support to promote their ability to manage their depression symptoms, then improve their psychological well-being and quality of life. The theoretical framework of the “Hi, Mom” is shown in Figure 2.

Self-efficacy, defined as the degree of one’s feelings about his/her ability to accomplish goals, was affected by four significant factors of mastery experience, vicarious experience, verbal persuasion, and physiological and emotional states [51]. Mastery experiences can be accumulated through past experiences. Vicarious experiences are obtained from the observation of others (i.e., role model) to achieve success in similar situations. Verbal persuasions are correlated with other person’s comments, feedback, and suggestion. Physiological and emotional states mean people’s physical and mental status. Social support is defined as the perception of possible received supports and the satisfaction with accepted assistances, comprising the structural and functional components [52]. Of which, the structural social support includes a formal social network (i.e., from health professionals) and informal social network (i.e., from family members, friends); while the functional social support is divided into informational support, material support, emotional support, and evaluation of support [53].

The “Hi, Mom” program of OTO intervention will integrate two face-to-face consulting sessions with online sessions including an information module, a communication module, an ask-the-expert module, and a peer story module over a period of three months. According to the self-efficacy theory, the mastery experiences of participants will be acquired by provision of the related PPD information via the information module, ask-the-expert module, and face-to-face consulting. Vicarious experiences of women can come from the peer support module where women may share their successful experience of dealing with PPD. Verbal persuasion can be gained from feedback, comments, and suggestions from health professionals in the ask-the-expert module and other mothers in the communication module. The physiological and emotional states can be improved through the above various supports, information and feedback in the information module, communication module, ask-the-expert module, peer story module, and face-to-face consulting. In terms of the social exchange theory, the structural social support, including the formal and informal social network of women, can be built; and various kinds of functional supports, such as informational support, material support, emotional support, and evaluation of support, can be provided from the health professionals and others through the designed information module, communication module, ask-the-expert module, peer story module, and face-to-face consulting.

The women in the control group will receive routine care, including health care from obstetricians and obstetric nurses during the hospitalization of three to five days; and at least two home visits from community health professionals [54]. The women in the intervention group will receive an OTO intervention called the “Hi, Mom” program and routine postpartum care. Table 1 describes the details of the “Hi, Mom” program.

The online session of the “Hi, Mom” program is designed to have fixed structures, which lasts approximately three months. Four modules are incorporated to meet learning needs, communication needs, emotional needs, and evaluation needs for rural-to-urban floating women. The information module is the PPD learning forum about prevention knowledge and skills showed by multimedia resources. In consideration of the lower educational level of floating women, we prefer to use many more pictures and videos, rather than words. The related knowledge and skills include (1) How to understand PPD? (2) How to deal with negative emotions? (3) How to relax yourself? (4) How to combat the stigma? (5) When and how to seek help? (6) How to balance postpartum life and family relationship? (7) How to adapt to the role of a mom? 

The communication module, ask-the-expert module, and peer story module will provide women with opportunities for acquiring social networking and various kinds of supports. For example, the communication module provides a platform for new mothers to tell their own postpartum stories, exchange experiences with PPD, and seek empathy and belonging. This module also invites women to discuss some topics such as the experience of “Doing the month”, communication barriers, potential interpersonal conflicts after childbirth, and effective skills to solve emotional problems. The ask-the-expert module gives floating women opportunities of timely interaction with health professionals where experts can answer women’s questions within 24 h. Some self-testing tools are likewise included in the module to assist new mothers in self-assessing their state of mind. The peer story module is the last module where six mothers are invited to share their successful experience of overcoming PPD and provide role models for these floating women. 

Floating women in the intervention group will be taught to log in and use each online module of the “Hi Mom” program. Women will be required to log into the online sessions at least twice a week, totaling at least one hour per week; and their duration and frequency of logins will be monitored to evaluate an individual’s adherence. Technical assistance for the online program will be available from Monday to Friday by telephone or email.

The offline session of the “Hi, Mom” program asks women to attend two face-to-face consulting meetings when the researchers conduct home visiting. Each face-to-face session will last an approximate length of 45–60 min, in which the researchers begin with mood checking and discussion of the women’s symptoms, then answer their questions, and provide face-to-face personalized, customized supports according to the various needs of each woman. 

Participants will receive phone reminders every week to motivate them to participate in the online and offline sessions. Risk assessment through both self-report of the women and the specific suicidal intention item on the EPDS questionnaire will be conducted during the intervention, postintervention, and at follow-up assessment. If the woman has a high risk of suicide, or a high likelihood of harming others, or develops severe depressive symptoms, she will be immediately referred to psychological or psychiatric health services, and her participation in the “Hi, Mom” program will end.

### 2.8. Measures

Table 2 presents the study variables and assessment time points.

#### 2.8.1. Social-Demographic and Clinical Data

Social-demographic and clinical data including maternal age, marital status, educational level, occupation, average monthly income, mode of childbirth, number of children, infant gender, infant feeding pattern, infant health, and infant fussiness will be collected through a questionnaire developed by the researchers.

#### 2.8.2. Primary Outcome

Postpartum depression symptoms as the primary outcome will be measured with the Chinese version of the Edinburgh Postnatal Depression Scale (EPDS). EPDS is composed of ten items and each item scores from 0 to 3 [55]. The total score ranges from 0 to 30, and the higher score indicates the more serious depressive symptoms. The reported internal consistency of the Chinese version EPDS was 0.87, and its concurrent validity was 0.79 with the BDI (Beck Depression Inventory) [56]. The total EPDS score of 10 or more is recommended as the presence of clinically relevant depressive symptoms in mainland China [56].

#### 2.8.3. Secondary Outcomes

Women perceived mental health-related stigma will be assessed by the Stigma-9 Questionnaire (STIG-9) [57]. The STIG-9 consists of nine items assessing cognitive, behavioral, and affective aspects of perceived mental health-related stigma. A four-point Likert scale will be used, i.e., disagree (0), somewhat disagree (1), somewhat agree (2), agree (3). Higher scores indicate stronger expectations of negative beliefs, feelings, and behaviors towards mentally ill people. The scale was found to have high internal consistency [57].

Postnatal social support scale (PSSS) will be used to assess Chinese women’s perception of received support in the postpartum period [58]. The 20-item tool is based on a four Likert-type point, being scored from 0 (never) to 3 (often). The total score of the PSSS is about 0–60. The higher score the mother has, implicates the more social support she receives. The reported internal consistency of this tool was 0.89 [58]. The test–retest reliability coefficient of PSSS was 0.92, and its content validity was 0.90.

Quality of life will be assessed with the Chinese version of the Euroqol Five-Dimension Scale (EQ-5D) [59]. It comprises five health dimensions (mobility, self-care, usual activities, pain/discomfort, and anxiety/depression), each with three response categories (no, some, or extreme problems) and a 0–100 points visual analogue scale (EQ VAS). The total score describes the health state, which is obtained through a fixed algorithm. The Chinese version of EQ-5D demonstrated an acceptable construct validity and test–retest reliability [59].

Mother–child bonding will be measured with the Chinese version of the Postpartum Bonding Questionnaire (PBQ) [60], which was developed to assess mother–infant bonding disturbances in the postpartum period. The 12-item instrument uses a six-point Likert scale ranging between 0 (never) and 5 (always). A lower score is indicative of a less impaired mother–child bond. The Chinese version of PBQ is found with good levels of internal consistency and validity and has been identified as a useful instrument for detecting mother–infant relationship impairments as perceived by Chinese women with PPD [60].

Women’s satisfaction with health care in the postpartum period will be assessed with a three-item questionnaire developed by the researchers. The items are “Overall, how satisfied with the healthcare your received?”, “Please give your reasons”, and “Please give your advice”.

### 2.9. Data Collection

Baseline assessments will be conducted by the research team and participants will be asked to complete EPDS, STIG-9, PSSS, EQ-5D, PBQ, and sociodemographic and clinical data in the obstetric wards. Postintervention assessment will be performed immediately after intervention and follow-up assessment will be performed 3 months after intervention. At the two time points of postintervention and follow-up assessment, the questionnaires, comprising EPDS, STIG-9, PSSS, EQ-5D, PBQ, and the health care satisfaction questionnaire, will be sent to participants by WeChat or email, and the completed questionnaires will be returned to the researchers likewise by WeChat or email. In order to improve the response rate, a reminder telephone or WeChat will be given to participants before and after one week of the two time points, respectively.

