### 2.5. Sample Size

The study sample size will be determined by the primary outcome of PPD, with the standardized effect size of 0.35 for PPD (EPDS scores) reported in a previous PPD trial [49,50]. A sample of 180 women (90 women per group) will be needed to detect an effect size of at least 0.35, with 80% power, two-sided *p* < 0.05, which is calculated by inputting the above parameters in PASS (Power Analysis and Sample Size) software (NCSS company, East Kaysville, UT, USA). Assuming an attrition rate of about 20%, a minimum of 226 women (113 in each group) is required.

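### Section 2.9 gives the 10-item primary EPDS no fallback when the 60-item remote packet is not returned: a cheap improvement, effective only if section 2.10 keeps EPDS-only returns

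*Protocol article*

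**What the plan says.** Section 2.9 (Data Collection) describes remote collection at both later time points: "the questionnaires, comprising EPDS, STIG-9, PSSS, EQ-5D, PBQ, and the health care satisfaction questionnaire, will be sent to participants by WeChat or email". Completed forms come back by the same routes. To raise the response rate, "a reminder telephone or WeChat will be given to participants before and after one week of the two time points, respectively". The section gives no order for the scales, no shortened request and no rule for a packet returned in part.

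Section 2.8.2 names the EPDS as the only primary outcome. Section 2.5 plans for loss: "Assuming an attrition rate of about 20%, a minimum of 226 women (113 in each group) is required".

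Section 2.10 analyses the EPDS together with stigma, social support, quality of life and bonding, over three time points, in one repeated-measures multivariate analysis of covariance. It describes no separate EPDS analysis and does not say how incomplete records are handled.

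Table 2 marks satisfaction with health care at postintervention only, whereas section 2.9 includes that questionnaire at both time points.

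**The concern.** The result of the trial rests on one short scale, yet that scale travels inside a packet six times its length and has no protection of its own. A woman with a young infant who will not face the whole packet might still answer ten items, but nothing in the described procedure asks her to. Each EPDS score lost costs power in a trial that has little to spare.

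Unequal response is also a realistic risk, because contact with the research team differs by arm. Section 2.7 says "Participants will receive phone reminders every week to motivate them to participate in the online and offline sessions", and Table 1 lists these calls, and the two consulting sessions, for the intervention group only. Control women also have at least two home visits, but from community professionals as part of routine care. If response differs by arm and silent women differ in mood, the EPDS comparison is distorted, and a larger sample would not correct that.

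Section 2.7 also uses one EPDS item, alongside self-report, for risk assessment at both time points. When the EPDS is not returned, that item is missing too.

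**Working it through.** **Length of the packet** (item counts from sections 2.8.2 and 2.8.3)
- EPDS: 10 ("EPDS is composed of ten items").
- STIG-9: 9 ("The STIG-9 consists of nine items").
- PSSS: 20 ("The 20-item tool is based on a four Likert-type point").
- EQ-5D: 5 dimensions plus 1 visual analogue scale.
- PBQ: 12.
- Satisfaction: 3, two of them open text.

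Sum: 10 + 9 + 20 + 5 + 1 + 12 + 3 = 60. The EPDS is 10/60 = 17%. Without satisfaction at follow-up, as in Table 2, the sum is 57.

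**The plan's own sample size** (section 2.5: d = 0.35, 80% power, two-sided 0.05)
- n per arm = 2 × ((1.96 + 0.842)/0.35)², which rounds up to 129 (130 with the exact t-test). The stated 90 is not reproduced.
- With 90 per arm, power = Φ(0.35 × √(90/2) − 1.96) = 65.1% (64.6% with the exact t-test).
- 90 can be reached only with an unstated assumption, for example adjustment for a baseline score correlated about 0.55 with the outcome.
- The attrition step does reproduce: 90/0.8 = 112.5, rounded up to 113 per arm, 226 in all.

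The sample-size mismatch is a separate matter. It matters here because it shows how little slack there is for lost EPDS scores.

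**Effect of an EPDS-only request.** Expected loss is 0.20 × 226 = 45.2 women. If a share r of them returns the short form, the number per arm with an EPDS is m = 113 × (1 − 0.20 × (1 − r)), and power is Φ(0.35 × √(m/2) − 1.96). The last column takes the plan's 80% at 90 per arm as given, by using a residual SD of √(1 − 0.546²).

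| r (assumed) | EPDS scores gained | m per arm | Power, plain comparison | Power if 90 per arm gives 80% |
|---|---|---|---|---|
| 0 | 0 | 90.4 | 65.3% | 80.2% |
| 10% | 4.5 | 92.7 | 66.4% | 81.1% |
| 25% | 11.3 | 96.0 | 67.9% | 82.5% |
| 50% | 22.6 | 101.7 | 70.4% | 84.6% |
| 100% (ceiling) | 45.2 | 113 | 74.9% | 88.1% |

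**Under the analysis in section 2.10.** Five outcomes at three time points make 15 scores per woman. If the multivariate model is run on complete cases, a woman who returns only the EPDS is still excluded and the gain is 0.

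**The case against.** The strongest objection is that the suggestion does not reach the planned analysis. Section 2.10 has no stand-alone EPDS comparison, and under a complete-case joint model an EPDS-only return adds nothing. It could even do harm, if a woman who would have sent the full packet late sends only the EPDS and so drops out of the model. This stands. It means that section 2.10 must change together with section 2.9.

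A reader might infer more from section 2.9 than it says, in four ways:
- *That the reminder asks again for the whole packet and that a partial return is lost.* The text states neither. This is a condensed article, and its silence on reminder content or partial returns is not an error.
- *That all of the 20% can be recovered.* Section 2.5 gives overall attrition, which can include withdrawals whom a shorter form will not reach. The 45 is an upper bound.
- *That a definite bias can be named.* For example, 15% against 25% non-response, with silent women 0.5 SD worse, would give 0.5 × 0.10 = 0.05 SD. But neither the non-response rates nor the difference in mood comes from the documents, and the assessment reminders go to all participants.
- *That the women cannot manage the questionnaires.* Section 2.7 says "In consideration of the lower educational level of floating women, we prefer to use many more pictures and videos, rather than words", but this concerns the content of the information module, not questionnaire burden.

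**Conclusion.** This is a worthwhile, low-cost design improvement, not a mistake in the text. Section 2.9 sets out a concrete procedure in which the single primary outcome is treated like every other scale, and the reminder is the only stated measure against non-response.

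The gain is modest: about 5 to 23 EPDS scores, and 1 to 5 points of power at d = 0.35 in a stand-alone EPDS comparison. This rests on three assumptions: a 20% loss at the time point analysed, a 10% to 50% return of the short form (no figure in the documents), and similar recovery in both arms. The gain is nil unless the analysis keeps women with an EPDS only. A reduction in bias is plausible and may matter more than the power, but the documents do not allow its size to be estimated.

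One discrepancy needs settling in any case: whether satisfaction is collected at follow-up (section 2.9) or not (Table 2).

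**What to change.** Two changes, to be adopted together:
1. **Section 2.9.** Place the EPDS first in the packet. At the existing contact one week after each time point, send every woman who has not replied, in both arms and in the same way, a separate EPDS-only form by the same WeChat or email route, while still inviting the full packet. Record which scores came by the short form.
2. **Section 2.10.** Analyse the EPDS on its own using all available EPDS scores, for example with a mixed model for repeated measures, which SPSS offers. State that a woman whose other scales are missing stays in this analysis.

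Also bring section 2.9 and Table 2 into line on when satisfaction is collected.

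Cost: a sentence or two in section 2.9, one short form made from an existing scale, and a rewritten primary-analysis statement in section 2.10. No new visit, staff or mode of administration is needed. The downside is that some late full returns may become EPDS-only, which costs a little secondary-outcome data. Continuing to invite the full packet limits this.

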### 2.10. Data Analysis

All the statistical analyses will be conducted by the Statistical Package for Social Sciences (SPSS). Descriptive analysis will be undertaken to describe the social-demographic and clinical data. Mean, standard deviation, and frequencies, as well as percentages will be used for continuous data and categorical data, respectively. The chi-square (χ^2^) for categorical variables, and the independent sample *t*-test for continuous variables will be conducted to detect any significant difference on social-demographic and clinical characteristics and baseline outcomes between the intervention group and the control group. The effect of intervention on reduced PPD symptoms and stigma and on improved social support, quality of life, and mother–child bonding across the three time points will be evaluated via repeated measures multivariate analysis of covariance to explore how outcomes have changed between groups, over time, and the interaction between group and time. The independent *t*-test will be used to compare satisfaction with the health care that they received in the postpartum period between the intervention group and the control group on the time point of immediately after the intervention. A *p* value less than 0.05 will be considered statistically significant.

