### 2.4. Study Setting and Recruitment

The research will be conducted in the maternity wards of three affiliated hospitals in X University, where each hospital has an annual baby-birth record of more than 4000. All women admitted in the wards will be approached by researchers to ask their willingness and will be measured by the EPDS before recruitment. If they have an EPDS of 10 or more, they will be eligible to participate in this study. The information sheets, posters, and leaflets will be used to introduce the purposes and process of the research before recruitment. If rural-to-urban floating women meeting the inclusion criteria are willing to participate, they will be asked to sign an informed consent form and be informed of freedom to withdraw whenever they want. The CONSORT (consolidated standards of reporting trials) [48] flowchart is illustrated in Figure 1. The recruitment period is expected to extend over a 3-month period. Recruitment of participants began in May 2022. Primary endpoints (baseline and postintervention), follow-up measure (three months), and data analysis are expected to be complete in January 2023.

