### 2.6. Randomization and Blinding

Participants will be randomly assigned to the intervention group or control group with an allocation ratio as 1:1. Sequence randomization will be performed using a computerized random number generator, and its result will be kept in sealed and opaque envelopes and saved by the researchers who have no direct relationship with the project to make sure that the random allocation is masked in advance. During the research process, the group allocation will be blinded to the participants, enrolling researchers, outcome assessors, and data analysts.

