**Figure 2 ijerph-19-07951-f002:**
[figure not shown]
The theoretical framework of the “Hi, Mom” intervention.

**Table 1 ijerph-19-07951-t001:** The details of the “Hi, Mom” program.

Items	Intervention Group	Control Group
Brief name	“Hi, Mom” + routine care	Routine care
Who provided	Researchers	Obstetricians, obstetric nurses, community doctors
Where	Web environment, home	Hospital, home
How (medium)	Online intervention by internet Offline intervention by face-to-face	Routine care by face-to-face
What	Information module; communication module; ask-the-expert module; peer story module; and face-to-face consulting.	Routine postpartum care, home visiting.
How long and how often	From childbirth to 3 month postpartum. The total intervention time not less than 12 weeks. Reminder telephones every week, reminding them to log in the online session at least twice a week, and no less than total 1 h per week; and attending 2 face-to-face consulting meetings, about 30–45min each time.	From childbirth to 1 month postpartum. At least 2 home visits.
When assessed	Baseline (preintervention) Postintervention (immediately after intervention) Follow-up (three months after intervention)	Baseline (preintervention) Postintervention (immediately after intervention) Follow-up (three months after intervention)

**Table 2 ijerph-19-07951-t002:** The study variables and assessment times.

Variables	Baseline (T0)	Postintervention (T2)	Three Months Follow-Up (T3)
Sociodemographic and clinical data	※		
Postpartum depression symptoms	※	※	※
Postpartum depression stigma	※	※	※
Social support	※	※	※
Quality of life	※	※	※
Mother–child bonding	※	※	※
Satisfaction with health care received		※	

T0: before randomization; T1: immediately after the intervention; T3: three months after the intervention.

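### Baseline EPDS is one of three outcome levels in the repeated-measures model and is not named as a covariate, so the treatment test has less power than conditioning on baseline would give

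*Protocol article*

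**What the plan says.** Section 2.10 (Data Analysis) evaluates EPDS and the other scales at all three assessments with a repeated-measures multivariate analysis of covariance. It lists effects of group, time and group-by-time, and marks none of them as the primary test. Table 2 gives the three assessments as baseline, postintervention and three-month follow-up, and its footnote defines the first as "T0: before randomization". Section 2.4 even counts baseline among the primary endpoints. Section 2.10 names no covariate.

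The same section plans chi-square and t-tests that "will be conducted to detect any significant difference on social-demographic and clinical characteristics and baseline outcomes between the intervention group and the control group".

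Section 2.5 sets the size: "A sample of 180 women (90 women per group) will be needed to detect an effect size of at least 0.35". The power and significance level behind this figure are 80% and a two-sided 0.05. The section does not mention baseline adjustment or a correlation between visits.

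**The concern.** A measurement taken before randomization cannot carry a treatment effect, so its expected difference between arms is zero. Used as an outcome level, it does harm in two ways.

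- The group main effect averages one visit with no effect and two visits that may have one. It therefore understates the treatment effect.
- The group-by-time test escapes that averaging. It instead subtracts a noisy baseline rather than conditioning on it, and spreads the signal over two degrees of freedom.

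Because no primary contrast is named, the diluted group effect could be reported as the result. The baseline significance tests add nothing: under sound randomization any difference that they find is due to chance.

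At stake is power in a trial that has little to spare, when the variable needed to recover it is already collected.

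**Working it through.** **Inputs.** From section 2.5: the sample size is planned "with the standardized effect size of 0.35 for PPD (EPDS scores) reported in a previous PPD trial", with 80% power, two-sided 0.05, and 90 evaluable women per arm. From section 2.6: allocation "with an allocation ratio as 1:1". Assumed, because the article does not give it: equal variances and a common within-woman correlation ρ of 0.3, 0.5 or 0.7 between any two visits. EPDS is taken alone.

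**1. The plan's own figure.** Unadjusted comparison of two means: n per arm = 2(1.960 + 0.842)²/0.35² = 128.1, so 129 (130 with the t distribution), not 90. At 90 per arm the noncentrality is 0.35/√(2/90) = 2.35 and power is about 65%. The attrition step does reproduce: 90/0.8 = 112.5, so 113 per arm and 226 in total. The size of the sample is a separate matter; it is used here only as the reference level.

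**2. Dilution of the group main effect.** With the same effect at both later visits: (0 + 0.35 + 0.35)/3 = 0.233. If the effect has gone by follow-up: (0 + 0.35 + 0)/3 = 0.117.

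**3. Power at 90 per arm, d = 0.35 at both later visits.** For the one-degree-of-freedom tests, λ = effect/√(2v/90), with v the variance factor, and power comes from the noncentral t. For group-by-time, λ = (90/2)(2d²/3)/(1 − ρ) = 3.675/(1 − ρ), and power comes from the noncentral F with 2 and 177 degrees of freedom.

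| Test | Effect | v at ρ = 0.3/0.5/0.7 | λ | Power |
|---|---|---|---|---|
| Group main effect, three levels, v = (1 + 2ρ)/3 | 0.233 | 0.533/0.667/0.800 | 2.14/1.92/1.75 | 57/48/41% |
| Group-by-time, 2 df | – | – | 5.25/7.35/12.25 | 52/67/88% |
| Postintervention EPDS adjusted for baseline, v = 1 − ρ² | 0.35 | 0.91/0.75/0.51 | 2.46/2.71/3.29 | 69/77/90% |
| Mean of both later visits adjusted for baseline, v = (1 + ρ)/2 − ρ² | 0.35 | 0.56/0.50/0.36 | 3.14/3.32/3.91 | 88/91/97% |

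The last row is the like-for-like comparator, since it uses the same visits as the plan's model.

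**4. Sensitivity.**
- Effect absent at follow-up: the group main effect has about 19/16/14% power. Group-by-time is unchanged at 52/67/88%, and the single adjusted visit at 69/77/90%. The adjusted mean falls to about 35/38/50%, because it now averages in a visit without effect.
- ρ = 0 with equal effects: the group main effect has 77%, the single adjusted visit 65%, and the adjusted mean 91%.

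**5. Baseline tests.** EPDS and the four secondary scales measured at baseline give five outcome tests. At 0.05 each, and if independent, the chance of at least one significant result under correct randomization is 1 − 0.95⁵ = 23%.

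**The case against.** **Dilution touches only one of the listed effects.** With a pre-randomization level in the model, group-by-time is the usual treatment test, and the zero at baseline is what it contrasts against. This stands. A reader might infer that the plan's treatment effect is necessarily diluted; the article does not say that the group main effect is that estimate.

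**Setting a two-visit test against one adjusted visit is not like for like.** This also stands. At ρ = 0.5 group-by-time and the single adjusted visit share the same noncentrality (7.35 = 2.71²), so the gap of 67% to 77% comes only from the extra degree of freedom. A one-degree-of-freedom contrast of baseline against the mean of the later visits, v = (1 + ρ)/2 + 1 − 2ρ, gives 63/77/94%, so baseline can remain a level and still match or exceed the single adjusted visit at the upper correlations. It remains below the adjusted mean of both visits (88/91/97%).

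**The correlation is assumed.** True. The entry rule of EPDS 10 or more (section 2.3) restricts the baseline range and may lower it. At ρ = 0.3, adjusting a single visit raises power only from 65% to 69% over an unadjusted comparison. At ρ = 0.7, group-by-time is within about two points of it.

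**A covariance analysis implies covariates, and the list may be in a fuller document.** Fair, so the missing list is not the point. The point is a choice the text does state: baseline as an outcome level.

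Two further inferences are tempting and unsupported. One is that the baseline tests will select the covariates; section 2.10 draws no such link. The other is that hospital is ignored. Section 2.4 says "The research will be conducted in the maternity wards of three affiliated hospitals", but section 2.6 describes no stratification by hospital, and centre adjustment is detail that an article may leave out.

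**Conclusion.** The point holds as one of efficiency and clarity. Baseline EPDS is an outcome level, no primary contrast is named, and the baseline outcomes are to be significance-tested.

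Over assumed correlations of 0.3 to 0.7 with an equal effect at both later visits, the group main effect and the group-by-time test both have less power than either baseline-adjusted analysis. Against the like-for-like adjusted mean, the shortfall is 31 to 56 percentage points for the group main effect and 9 to 36 for group-by-time. Against a single adjusted visit, it is 12 to 49 and 2 to 17.

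These sizes rest on the assumed correlation, equal variances and a lasting effect. If the effect fades by follow-up, the adjusted mean loses its advantage over group-by-time, while the adjusted postintervention visit keeps its own. The baseline tests are uninformative, but they do not by themselves alter any treatment estimate.

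**What to change.** - Use only the postintervention and follow-up visits as outcome levels, with baseline EPDS as a pre-specified covariate. Treat each secondary scale measured at baseline in the same way, with its own baseline value.
- Name one primary contrast: EPDS at postintervention, or the mean of the two post-baseline visits. The first is safer if the effect may fade; the second has more power if it lasts.
- Present baseline characteristics and scores by arm descriptively, and delete the chi-square and t-tests on them.
- State the correlation assumed when power is quoted for the adjusted analysis. For a single visit, 90 per arm reaches 80% power only if ρ is about 0.55 or more (√(1 − 90/128.15) = 0.546), so adjustment alone may not restore the stated power.

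The cost is a change of wording in section 2.10, with a matching correction where section 2.4 lists baseline as an endpoint. No new data are needed: section 2.9 already collects EPDS, STIG-9, PSSS, EQ-5D and PBQ at baseline.
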